**Figure 1 figure1:**
[figure not shown]
Swab positivity by week in the English national sentinel surveillance network from March 2022 to January 2023 [4]. hMPV: human metapneumovirus; RSV: respiratory syncytial virus.

In the context of a postpandemic health care service where there are high levels of circulating influenza, accurate, rapid molecular diagnostic test platforms have the potential to (1) improve clinical decision-making regarding the use of antibiotics and antivirals, (2) improve patient outcomes due to the early appropriate use of antivirals, and (3) provide better information to inform sentinel surveillance and clinical research including studies of vaccine effectiveness and real-world trials [5,6].

Specifically, for patients with influenza infection, early diagnosis and administration of antivirals may improve clinical outcomes [7,8]. They may also limit symptom duration and spread to household contacts, and newer antivirals for influenza, such as baloxavir, have been shown to improve the time to resolution of symptoms and reduce complications in high-risk patients [9].

Currently, only a small proportion of patients with respiratory tract infections (RTIs) undergoes diagnostic microbiological testing before receiving treatments in primary care [10], and there is evidence of widespread variations in antimicrobial prescribing practices [11]. This is important, as prescribing in primary care accounts for about 8% of National Health Service (NHS) expenditure, which is equivalent to over £9 billion (US $11.1 billion) per year, with just over £220 million (US $271.5 million) being spent on antimicrobials [12]. Inappropriate prescribing of antimicrobials and unwarranted variation in prescribing can contribute to increase of antimicrobial-resistant strains and patient adverse events in the short and long term [13].

We have previously shown that, in a prepandemic context, it is feasible to undertake point-of-care testing (POCT) for influenza in primary care in the England, with promising impacts on antimicrobial use and estimates of influenza vaccine effectiveness that are comparable with published data [14-16]. However, its impact on more severe outcomes such as hospitalization and mortality following infection has not been reported.

Recent work on in-pandemic prescribing of azithromycin and doxycycline for RTIs across the sentinel network has shown scope for measures to improve antibiotic stewardship in primary care [17].

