## Methods

### Study Setting and Population

The impact of POCT for influenza on antimicrobial stewardship (PIAMS) study will take place between December 2022 and May 2023, during the influenza season as defined by the UK Health Security Agency (UKHSA). It is nested within the English national sentinel network managed by the Oxford-Royal College of General Practitioners (RCGP) Research and Surveillance Centre (RSC) at the Nuffield Department of Primary Care, University of Oxford. This network of over 1800 primary care practices is the primary infectious disease surveillance network for England, which is generally representative of the English population [19]. It has been providing weekly infection data for over 50 years that are used to monitor trends in infectious disease and investigate real-world vaccine and treatment effectiveness [20].

All practices that contribute data to the English national sentinel network will be invited to participate in the PIAMS study, and 10 practices will be selected to take part in the PIAMS study. We will prioritize practices within the network with capacity to undertake influenza POCT and who had previously been involved in SARS-CoV-2 POCT through the RAPTOR-C19 study [21]. Those practices that have a history of less than 80% complete data returns during the previous winter season will be excluded.

Each participant practice will receive training about the study, including hands-on training on how to administer a swab test and how to use the POCT analyzers.

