### Statistical Methods

We will undertake descriptive analysis of the swabbing rates and swab positivity rates from the study practices. This includes analysis of the demographic and clinical characteristics of those presenting with RTI symptoms and those with confirmed influenza infections in primary care. We will also report the number of patients who have also undertaken swabbing for reference laboratory analysis in addition to POCT testing in study practices. In those study practices that also take part in virological surveillance, these reference laboratory swabs are reported to the UKHSA as part of national disease surveillance.

To answer our primary objective, we will calculate the crude odds of antimicrobial prescribing (all antibiotics and all antivirals regardless of type), given a POCT diagnosis of influenza is the probability of antimicrobial prescribing given a particular POCT test result. We will record whether the antimicrobials were given within 7 days of the POCT diagnosis or within 30 days of diagnosis. We will calculate the crude odds ratio by dividing the odds of antimicrobial prescribing in people who receive a positive influenza POCT result by the odds in people who receive a negative test result.

We will also calculate the adjusted odds ratio using a logistic regression model. We will use the following set of covariates that are known to be associated with the severity of influenza and are collected from the routine data extracted from the electronic health record: age, sex, ethnicity (reported in 5 categories: White, Asian, Black, other, or mixed; maximized using an ontology [30]), socioeconomic status (measured using the index of multiple deprivation [31], which is a nationally available measure assigned based on post code), any of these chronic underlying conditions (chronic pulmonary disease, cardiovascular disease, diabetes, liver disease, renal disease, neurologic or neuromuscular conditions, treatment-induced immunosuppression, and disease-induced immunosuppression), number of GP visits in the 12 months prior to the study period describing a study participant’s health care–seeking behavior, number of hospitalizations in the 12 months prior to the study period (used as proxy for the severity of the chronic conditions), influenza vaccination in previous influenza seasons (at least one), pregnancy, use of influenza antivirals, and pneumococcal and COVID-19 vaccination status.

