### Limitations

The nonrandomized design is a limitation of our study. However, we feel that there is still value in examining the objectives within this study using a mixed methods approach as there are many questions about the challenges and barriers to implementation of rapid diagnostic testing in primary care, including the variability of adoption in different practices that are important to understand [15]. Unpacking these factors using a mixed methods design will be important to design a successful experimental study at scale to answer questions related to health outcomes. Additionally, information about influenza subtype is not available from the POCT machines used in this study and will restrict interpretation of our results, especially for calculating influenza vaccine effectiveness. A possible solution to this would have been to ask study practices to send their swabs to the national reference laboratory for additional analysis. However, this would have introduced a further step in the testing procedure in the clinic, which may have increased the risk of aerosol generation. Given that the study was originally proposed during the COVID-19 pandemic, we felt it was important to minimize the risk of generating aerosol droplets and thus did not include this in the study.

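### The adjusted model controls for influenza vaccination in earlier seasons but not in 2022-2023, so the vaccination closest to the test result is controlled only through partial proxies

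*Protocol article*

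**What the plan says.** All references are to the Protocol article. Under Statistical Methods the primary objective is addressed first by a crude odds ratio, described as "dividing the odds of antimicrobial prescribing in people who receive a positive influenza POCT result by the odds in people who receive a negative test", and then by a model: "We will also calculate the adjusted odds ratio using a logistic regression model". The covariates are introduced with "We will use the following set of covariates that are known to be associated with the severity of influenza" and then listed in full, without wording that would make the list illustrative.

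The vaccination terms come at the end: "influenza vaccination in previous influenza seasons (at least one), pregnancy, use of influenza antivirals, and pneumococcal and COVID-19 vaccination status". Influenza vaccination is therefore defined by earlier seasons only, as any versus none. The same list also contains age, sex, ethnicity, deprivation, a set of chronic conditions, GP visits in the preceding 12 months (as a measure of care-seeking) and hospitalizations in the preceding 12 months (as a proxy for the severity of chronic disease).

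Study Setting and Population says that the study "will take place between December 2022 and May 2023, during the influenza season as defined by the UK Health Security Agency". No section adds vaccination in that season to the model.

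**The concern.** Leaving current-season vaccination out of the covariates is natural when vaccination is the exposure, as in a vaccine-effectiveness analysis. Here the exposure is the influenza test result and the outcome is antimicrobial prescribing. Vaccination in the current season is then a pre-test characteristic that plausibly changes the probability of a positive result. The article accepts that link in its Introduction, where earlier point-of-care testing in this setting is said to have given "estimates of influenza vaccine effectiveness that are comparable with published data".

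Vaccinated patients would be over-represented among the negatives. If, at the same age, morbidity and consultation history, they are also prescribed antibiotics more often, the odds ratio for a positive result falls below what the result itself explains. For antibiotics, that bias favours the stewardship effect the study hopes to see. An indicator of at least one earlier vaccination cannot separate a patient vaccinated in autumn 2022 from one vaccinated once some years ago.

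**Working it through.** The plan gives no figure to reproduce on this point. The first check is of the text; the second is an illustration in which every input is assumed.

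**Text.**
- Influenza vaccination in the list: earlier seasons only, at least one.
- Other vaccines in the list: pneumococcal and COVID-19.
- Season of the exposure: December 2022 to May 2023.
- Vaccination in 2022-2023: not in the list or elsewhere in the analysis text.

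**Illustration before any adjustment.** Assume half the patients are vaccinated this season (V) and half are not (U), and that the test result has no effect on antibiotic prescribing within either group. Let p be positivity and r the antibiotic proportion. Then:

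- proportion prescribed in positives = (0.5·p_U·r_U + 0.5·p_V·r_V) / (0.5·p_U + 0.5·p_V)
- the same for negatives, with 1 − p in place of p
- apparent OR = odds in positives / odds in negatives

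*Scenario 1:* p_U = 0.30, p_V = 0.20, r_U = 0.20, r_V = 0.26.
- Positives: (0.030 + 0.026)/0.25 = 0.224
- Negatives: (0.070 + 0.104)/0.75 = 0.232
- Difference −0.8 points; OR = (0.224/0.776)/(0.232/0.768) = 0.96

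*Scenario 2:* p_U = 0.30, p_V = 0.15, r_U = 0.18, r_V = 0.28.
- Positives: (0.027 + 0.021)/0.225 = 0.213
- Negatives: (0.063 + 0.119)/0.775 = 0.235
- Difference −2.2 points; OR = (0.2133/0.7867)/(0.2348/0.7652) = 0.88

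**Wider range.** Assume coverage of 30-70%, odds of a positive test lowered by 20-60% in the vaccinated, a prescribing OR for vaccination of 1.0-2.0, and baseline positivity and prescribing of 30% each. A true OR of 1.00 then appears as 0.86 to 1.00. The value is 0.95 at 50% coverage, a 40% reduction and a prescribing OR of 1.5. It is exactly 1.00 wherever the prescribing OR for vaccination is 1.0.

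**What the earlier-season flag alone recovers.** Logistic regression of prescribing on test result and flag, fitted to the expected cell proportions, assuming 90% of this season's vaccinated carry the flag:

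| Flag present in this season's unvaccinated | Scenario 1 OR | Scenario 2 OR |
|---|---|---|
| 20% | 0.98 | 0.94 |
| 40% | 0.97 | 0.91 |
| 60% | 0.96 | 0.90 |

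On the log-odds scale the flag removes about half of the shift in the first row and about a tenth in the last. Adding the current-season term returns 1.00 in every case.

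**Scale against sampling error.** With 1,000 patients, the most the Sample Size Calculation section expects, the standard error of the log OR in Scenario 2 is √(1/48 + 1/177 + 1/182 + 1/593) = 0.18. In Scenario 1 it is 0.17. A null 95% interval would run from about 0.7 to 1.4. After the flag, the residual shift in the table is about 0.1 to 0.6 standard errors. Adding the current-season term as well as the flag takes the standard error from the crude 0.1746 to 0.1762 (Scenario 1) and from 0.1835 to 0.1878 (Scenario 2), a rise of about 1% and 2%.

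**The case against.** The strongest reply is that the main confounding path is already blocked. Current-season vaccination would be linked to prescribing chiefly because it marks older, sicker and more frequently consulting patients. Age, the chronic conditions, pregnancy, GP visits, prior hospitalizations and the other vaccine terms are all in the model. A variable that, given these, affects only the exposure is not a confounder. The remaining route, through the clinician's prior expectation of influenza, has little room once an accurate PCR result is available in under 20 minutes. Much of this stands. It limits the size of the problem, though it does not show that the remaining association is zero.

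It is also fair that the illustrations use inputs found nowhere in the documents, start from a model with no other covariates, and treat antibiotics only, whereas the planned outcome includes antivirals. They are upper bounds for the chosen inputs and say nothing about the antiviral odds ratio.

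Three stronger readings are tempting and not supported. A reader might infer that influenza vaccination is left uncontrolled; it is controlled through partial proxies. A reader might infer that current-season vaccination has been shown to confound this contrast; that needs an association with prescribing, given the other covariates, which the documents do not report. A reader might also take the Limitations remark that missing subtype data "will restrict interpretation of our results, especially for calculating influenza vaccine effectiveness" as evidence that the covariate list was built for another analysis. That remark concerns influenza subtype and says nothing about covariate choice.

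**Conclusion.** The gap in the text is real. It is not detail left to a fuller document, because the list is closed and specific enough to define the influenza vaccine term as at least one earlier season. What follows is limited: the vaccination most directly related to the test result is controlled only indirectly, and any residual confounding of the positive-versus-negative odds ratio is probably modest.

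Under the assumed inputs and before any adjustment, a true antibiotic OR of 1.00 would appear as about 0.88 to 0.96. The listed covariates would bring it closer to 1.00, and it would equal 1.00 if vaccination is unrelated to prescribing given those covariates. The direction, below 1, rests on the assumption that vaccinated patients are less often positive and more often prescribed antibiotics. The case for the change is that it is nearly free in the adjusted analysis of the primary objective. No large bias has been demonstrated.

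**What to change.** In the covariate list under Statistical Methods, add: 2022-2023 seasonal influenza vaccination recorded before the swab date (yes/no). Keep the earlier-season term beside it. Dating the vaccination before the swab ensures that the covariate precedes the exposure. If the word previous was intended to include the current season, correct the wording so that the season and the cut-off date are explicit.

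The cost is one degree of freedom and possibly a slight loss of precision (about 1-2% on the standard error in the illustrations above). The information is expected in the same routine record extract that supplies the earlier-season term, so no new data collection should be needed.

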**Results:**

We will present the crude and adjusted odds of antimicrobial prescribing (all antibiotics and antivirals) given a POCT diagnosis of influenza, stratifying by whether individuals have a respiratory or other relevant diagnosis (eg, bronchiectasis). We will also present the rates of hospital referrals and deaths related to influenza infection in PIAMS study practices compared with a set of matched practices in the sentinel network and the rest of the network. We will describe any difference in implementation models in terms of staff involved and workflow.

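### Antiviral use is an undated covariate in the adjusted model although antivirals are part of the outcome; under a same-episode reading the adjusted odds ratio answers a different question from the crude one

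*Protocol article*

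**What the plan says.** All of this is in the Statistical Methods section of the protocol article unless noted.

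- **Outcome.** For the primary objective, the plan analyses "antimicrobial prescribing (all antibiotics and all antivirals regardless of type"). On timing it adds: "We will record whether the antimicrobials were given within 7 days of the POCT diagnosis or within 30 days of diagnosis". The Results paragraph of the abstract carries the same outcome into the adjusted analysis: "crude and adjusted odds of antimicrobial prescribing (all antibiotics and antivirals) given a POCT diagnosis of influenza".
- **Contrast.** The crude odds ratio divides the odds of prescribing "in people who receive a positive influenza POCT result by the odds in people who receive a negative test result".
- **Model.** "We will also calculate the adjusted odds ratio using a logistic regression model". One covariate list follows, introduced as factors linked to influenza severity and taken from the routine record. It closes with "pregnancy, use of influenza antivirals, and pneumococcal and COVID-19 vaccination status".
- **Dating of covariates.** Three items are tied to an earlier period: GP visits in the preceding 12 months, "number of hospitalizations in the 12 months prior to the study period", and "influenza vaccination in previous influenza seasons (at least one"). Antiviral use is not dated. Nor are chronic conditions, immunosuppression, pregnancy, or pneumococcal and COVID-19 vaccination.
- **A different primary outcome elsewhere.** The Sample Size Calculation section names antibiotic prescribing alone as the primary outcome measure.

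**The concern.** Antivirals appear on both sides of the adjusted model, and nothing in the article separates the two in time. An analyst who codes the covariate from prescriptions in the same episode would condition on a component of the outcome. That component is also a consequence of the exposure, because a positive result is what would prompt an antiviral.

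At stake is the meaning of the adjusted estimate for the primary objective. The article's Introduction presents better-informed use of antibiotics and antivirals as a reason for rapid testing. An adjusted odds ratio with the antiviral response taken out no longer measures the effect that the crude one measures. A reader comparing the two would probably put the gap down to confounding by age, comorbidity and so on, when much of it could come from this one covariate.

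**Working it through.** The article gives no figure for this model, so there is none to reproduce. The check has three parts.

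**1. Structure.** Let T be the POCT result, B any antibiotic, V any antiviral in the outcome window, and Y = 1 if B = 1 or V = 1.

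- If the covariate is V itself, then V = 1 implies Y = 1, and the cell with V = 1 and Y = 0 is empty. This is quasi-complete separation: the maximum-likelihood coefficient for V is infinite.
- People with V = 1 then carry no information about T. The coefficient for T is estimated from people with V = 0, and for them Y = B. The adjusted POCT odds ratio is therefore the antibiotic odds ratio among people given no antiviral.

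**2. Size.** No prescribing rates are in the article, so these are assumptions: antibiotics 25% in positives and 40% in negatives; antivirals 1% in negatives and a = 10%, 30% or 50% in positives; antibiotic and antiviral prescribing independent within each test group.

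- Composite risk in negatives: 1 − 0.60 × 0.99 = 0.406; odds 0.406/0.594 = 0.684.
- Composite risk in positives: 1 − 0.75 × (1 − a).
- Adjusted limit for any a: (0.25/0.75)/(0.40/0.60) = 0.50.

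| Antivirals in positives | Composite risk, positives | Odds, positives | Crude odds ratio | Adjusted odds ratio |
|---|---|---|---|---|
| 10% | 0.325 | 0.481 | 0.70 | 0.50 |
| 30% | 0.475 | 0.905 | 1.32 | 0.50 |
| 50% | 0.625 | 1.667 | 2.44 | 0.50 |

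The crude odds ratio equals 1 when 0.75 × (1 − a) = 0.594, that is a = 0.208. Under these rates the crude and adjusted estimates point in opposite directions only when more than about 21% of positives receive an antiviral.

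**3. Simulation under the same rates.** These were single data sets of 1000 people (the article's maximum), with an influenza share of 20%, 26% or 36%. The last two are guided by Table 1 (215/818 = 26%) and the abstract (36%). Both are shares of positive virology, so they are only a rough guide.

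- There were 19 to 205 antiviral users per data set, and none lacked the outcome.
- The antiviral coefficient was about 12, 22 and 32 after 10, 20 and 30 iterations. These values only show where the algorithm was stopped.
- The POCT odds ratio was the same at all three stopping points and equal to the odds ratio among people with no antiviral.
- With 1,000,000 people, a 30% antiviral rate in positives and 1% in negatives, the crude odds ratio was 1.33 and the adjusted one 0.50, in line with the table.

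**Other readings**

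| Outcome and covariate | Separation | Consequence |
|---|---|---|
| Composite outcome, same-episode use | Quasi-complete | POCT odds ratio changes meaning |
| Antivirals as a separate outcome, same-episode use | Complete | Covariate is the outcome |
| Antibiotics only, same-episode use | None | Still adjusts for a post-test variable |
| 7-day outcome, use counted over a longer post-test window | Not perfect | Still adjusts for a post-test variable |
| Use before the test (simulated as unrelated to the outcome) | None; standard error about 0.3 at 1000 people | POCT odds ratio essentially unchanged |

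**The case against.** The strongest reply is that history of antiviral use was meant. The list is drawn from the routine record and described in terms of severity. The items next to antiviral use (pregnancy and vaccination status) are undated too, and a look-back window is the kind of detail an article leaves to a fuller plan. That is fair as far as it goes: the lack of a date is not peculiar to this item, and same-episode use is not stated. But this is the undated item that names a component of the outcome, and the article itself fixes the outcome, the model and the list. Nothing in it excludes the harmful reading.

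It can also be said that the article does not settle whether antibiotics and antivirals form one composite, and that its sample size section uses antibiotics only. This stands against any unconditional claim of perfect prediction. It does not rescue the covariate, because under each outcome definition same-episode use follows the test result.

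A reader might infer that the model fails altogether. It does not: only the antiviral coefficient diverges, and the POCT odds ratio remains finite. A reader might also infer that the adjusted result must reverse the crude one. The documents give no prescribing rates to support that, and with 10% antiviral use in positives both estimates are below 1 (0.70 and 0.50).

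Finally, the crude odds ratio, the sample size and the between-practice comparison are untouched. That is correct and limits the reach of the point.

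**Conclusion.** The point holds in conditional form. As written, the adjusted model may be fitted with a covariate that is both part of the outcome and a consequence of the test result, and no text prevents it.

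If same-episode use is coded and the outcome is the composite, the change in what the POCT odds ratio estimates is certain, because it follows from the definitions. Its size depends on rates that the article does not give. Under the assumed ones, a crude odds ratio anywhere from about 0.70 to 2.44 is reported as about 0.50 after adjustment, and a change of direction is possible but not guaranteed. The constant 0.50 also rests on the independence assumption; without it, the adjusted value is whatever the antibiotic odds ratio is among people given no antiviral.

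If the outcome is antibiotics only, the defect reduces to adjustment for a post-test variable. If prior use was intended, there is no defect beyond the missing words.

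**What to change.** Delete antiviral use from the covariate set. If earlier use was intended, define the item as an influenza antiviral prescription dated before the index swab, with a stated look-back period. Add one sentence requiring every covariate in the list to be measured before the swab, which also settles the other undated items.

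The cost is one phrase removed or dated and one sentence added. The sample size, the data collection and the crude analysis stay as they are.

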To answer our secondary objective, we will select a matched set of practices from the rest of the English national sentinel network based on practice size, average age of registered patients, proportion of registered female patients, and number of GPs employed during the study.

The rates of hospital referrals and deaths related to influenza infection within 30 days of diagnosis will be compared between PIAMS study practices and the rest of the network using the ANOVA test.

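### The Methods select matched practices for the severe-outcome objective, but the stated ANOVA compares study practices, unadjusted, with the rest of the network; the Abstract names both comparators

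*Protocol article*

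**What the plan says.** All of this is in the protocol article.

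- **Statistical Methods, matching.** To answer the secondary objective, "we will select a matched set of practices from the rest of the English national sentinel network based on practice size". The full list of matching variables is "based on practice size, average age of registered patients, proportion of registered female patients, and number of GPs employed during the study".
- **Statistical Methods, test.** The next sentence says that 30-day rates of influenza-related hospital referral and death "will be compared between PIAMS study practices and the rest of the network using the ANOVA test". It names no covariates and does not mention the matched set.
- **Abstract, Results.** The same rates will be "compared with a set of matched practices in the sentinel network and the rest of the network".
- **Study Setting and Population.** All network practices are invited and "10 practices will be selected to take part in the PIAMS study". On selection: "We will prioritize practices within the network with capacity to undertake influenza POCT and who had previously been involved in SARS-CoV-2 POCT". Also: "Those practices that have a history of less than 80% complete data returns during the previous winter season will be excluded".
- **Statistical Methods, covariates.** Deprivation, chronic conditions, hospitalizations in the prior 12 months and other covariates are introduced as related to how severe influenza is. They are used only in the logistic model for antimicrobial prescribing.
- **Objectives and Limitations.** Severe outcomes are to be described, and the absence of randomization is acknowledged in general terms.

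**The concern.** The matched set is selected for this objective, yet the only test the Methods state for it uses a different, unmatched comparator. An analyst working from the Methods would run one analysis, and an analyst working from the Abstract would run at least two. Neither section says which contrast is the main one.

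The choice matters because of how the 10 practices enter the study. Practices with spare capacity, earlier research testing and good data returns may also differ in patient mix, referral habits or completeness of recording. An unadjusted contrast with the whole network leaves any such difference in the result. A reader could then take a difference in referral or death rates, or its absence, as telling them something about POCT when it partly reflects which practices took part.

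**Working it through.** The article gives no event rate, between-practice spread, power or sample size for referrals or deaths. There is no figure to reproduce, so the check sets the sections side by side.

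**Step 1. Which comparator?**

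| Place | Matched set | Rest of network | Method |
|---|---|---|---|
| Abstract, Results | yes | yes | none named |
| Statistical Methods, matching sentence | selected | source of the matches | none |
| Statistical Methods, test sentence | not mentioned | yes | ANOVA, no covariates |

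The Abstract and the test sentence disagree, and the Methods give the matched set no analysis.

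**Step 2. Does the matching cover what drives selection or severity?**

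| Variable | Used to select or screen study practices | Linked by the article to influenza severity | In the matching list | Adjusted for in the severe-outcome test |
|---|---|---|---|---|
| Testing capacity | yes | no | no | no |
| Earlier SARS-CoV-2 POCT | yes | no | no | no |
| Data returns of at least 80% | yes | no | no | no |
| Deprivation | no | yes | no | no |
| Chronic conditions | no | yes | no | no |
| Prior-year hospitalizations | no | yes | no | no |
| Age | no | yes | yes (practice average) | no |
| Sex | no | yes | yes (proportion female) | no |
| Practice size, number of GPs | no | no | yes | no |

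None of the three selection criteria is a matching variable. Of the severity covariates shown, age and sex are matched; deprivation, chronic conditions and prior hospitalizations are not.

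**Step 3. What does each contrast estimate?** Write the expected difference in mean practice rate as D = A + S. Here A is the association with POCT use and S is the difference that would exist without POCT.

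- Against the rest of the network, D = A + S, with S wholly unadjusted.
- Against the matched set, the part of S carried by size, age, sex and GP count is largely removed. The remainder stays.
- Adding deprivation to the matching or to a model removes a further part.

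The ANOVA estimates D. Nothing in it separates A from S. The direction and size of S are unknown.

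**Step 4. Would a three-group ANOVA resolve it?** If PIAMS, matched and remaining practices were the three groups, the overall F test would ask whether three means are equal. A significant result could come from matched versus remaining practices, which says nothing about POCT. It would also ignore the matching and leave the main contrast unnamed.

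**Step 5. Is better matching feasible?** The article gives 1879 practices in the network by October 2021. Removing the 10 study practices leaves 1879 − 10 = 1869 candidates, about 187 per study practice (1869 / 10).

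**The case against.** The strongest reply is that the test sentence has simply lost a phrase. The matched set is selected expressly for this objective, the Abstract names both comparators, and ANOVA is a natural choice for three groups. This is plausible. A reader might infer that the matched comparison has been abandoned, and the document as a whole does not support that. What stands is that the Methods, read alone, state only the unmatched test, and that no section names the main contrast.

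A second reply is that no causal claim is planned. The objective is to describe severe outcomes, the Limitations concede non-randomization, and questions about health outcomes are left to a later experimental study. This also has force: a descriptive objective can be met without isolating a POCT effect, so it would be wrong to say the secondary question goes unanswered. But the Introduction does speak of impact on severe outcomes, a significance test between testing and other practices goes beyond description, and the Limitations do not discuss how practices were selected.

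A third reply is that nothing in the article shows the selection criteria to be related to referral or death rates. That is correct, and it limits the point to a possible bias of unknown size. It is tempting to size the bias from the between-practice coefficient of variation of 0.23 in the sample size section. That figure is for antibiotic prescribing. It describes ordinary variation between practices, which an ANOVA with practices as units already carries in its error term, and it does not measure selection bias.

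Finally, the four matching variables are defensible structural features. Adding deprivation improves the design; its absence is not an error in itself.

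**Conclusion.** The point holds as a contradiction over the comparator with a practical consequence. If the Methods are followed literally, the matching is set aside and 10 prioritized, screened practices are compared, unadjusted, with an unmatched network. That contrast could confuse practice differences with an association with POCT. This rests on one assumption the article cannot confirm: that practices with testing capacity, earlier POCT experience and good data returns differ from others in ways related to referral or death.

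The size of any bias cannot be derived from the document, and none is claimed here. Nor does the document support saying that the authors will report a POCT effect, or that the matched set has been replaced by design. The matter concerns a secondary, mainly descriptive comparison. It is worth correcting because the correction is cheap and the current text leaves the main contrast open.

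**What to change.** 1. Reconcile the Abstract with Statistical Methods so that both name the same comparators.
2. State that PIAMS versus matched practices is the main comparison for referrals and deaths, with the rest of the network shown as context.
3. Add practice-level deprivation to the matching list or to a practice-level model. The index is already extracted for the prescribing model and needs only averaging by practice. Prior-year all-cause hospitalization is an optional addition.
4. Report the result as an association, and mention practice selection in the Limitations.

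Matching on each practice's influenza referral or death rate from the previous winter is not advised. The Abstract says pandemic measures disturbed influenza patterns in 2021, and the Introduction contrasts autumn 2022 with 2021, so practice-level counts from that winter would be a sparse and disturbed baseline.

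The cost is a few sentences and one or two variables, which must also be compiled for the candidate comparison practices. The downside is slightly fewer close matches, with over 1800 practices to draw from. Better matching reduces confounding by practice differences but does not remove it.
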